## Abstract

Chronic visceral pain affects over 20% of adults globally but remains poorly understood, significantly impacting quality of life and healthcare costs. Limited understanding and diagnostic misconceptions hinder effective management, particularly during acute pain flares. This study aims to clarify underlying mechanisms and improve clinical management by combining detailed phenotyping, genetic analysis, immunological profiling, pain mapping, and wearable sensor data in three cohorts: Extreme Visceral Pain, Lack of Visceral Pain, and Healthy Controls. Participants with diverse visceral conditions, such as polycystic kidney disease, inflammatory bowel disease, chronic pancreatitis, endometriosis, painful bladder syndrome, vaginal mesh complications, and fibromyalgia, are recruited via clinical referrals from NHS Cambridge University Hospitals and NHS Lothian. Healthy control volunteers are recruited locally. Data collection involves daily pain ratings captured through a mobile app, wearable physiological monitoring, quantitative sensory testing, detailed medical and lifestyle questionnaires, and bio-sample analyses (genetic variants, autoantibodies). The primary confirmatory outcome evaluates the correlation between wearable sensor parameters and self-reported visceral pain intensity. Genetic analyses, including functional SNP allele discovery and Mendelian gene effect analysis, and immunological profiling will explore underlying biological mechanisms. Challenges anticipated include potential compliance and technical difficulties in remote data collection, potentially affecting data quality. Findings will be disseminated widely, aiming to refine diagnostic tools and inform treatment strategies, ultimately enhancing patient care and outcomes in chronic visceral pain management.

## Introduction

Chronic visceral pain originating from the chest, abdomen and pelvis organs, is estimated to affect up to 25% of the adult world population [1], and imposes a significant economic burden on global healthcare systems [2], with annual costs exceeding $50 billion in the US for chronic visceral pain and £100 million in the UK for abdominal pain alone [3]. Beyond the economic toll, this kind of pain disrupts essential daily activities such as urination, defecation, and sexual intercourse. Unpredictable episodes of severe visceral pain, known as “flares”, often require hospitalization and are a common challenge across various visceral pain conditions [4,5].

Despite its prevalence and impact, our scientific understanding of visceral pain remains surprisingly limited. Psychological factors are known to play a role in maintaining chronic pelvic or urogenital pain, with stress being a recognized aggravator of it. Yet, these biological associations are poorly understood and are often misinterpreted, which hinders proper diagnosis and treatment. Equally unclear is the relationship between the level of pain experienced by patients and the severity of their underlying visceral disorder. Pain often persists even when the visceral pathology is adequately treated, such as during remission in conditions like ulcerative colitis [6] or following surgery for endometriosis [7].

There are significant gaps in our knowledge of basic visceral pain mechanisms. For example, we lack detailed information on the sensory innervation of key tissues like the kidney and uterus, and the roles of the vagus and peripheral nerves in visceral pain remain unclear. Currently, there are no specific analgesics for visceral pain; the most prescribed drugs are antispasmodics, while conventional analgesics like opioids and nonsteroidal anti-inflammatory drugs (NSAIDs) are associated with problematic side effects. Psychological approaches, although beneficial, are typically designed for musculoskeletal pain and do not adequately address the unique concerns of visceral pain patients [8].

Most diagnoses of visceral pain are based on the presumed origin of the pain within specific organs. However, there is a scarcity of data on the physiological and behavioural changes that accompany visceral pain episodes, particularly in natural, free-living conditions. Currently available pain assessment tools designed for musculoskeletal and neuropathic pain fail to adequately capture the complexity, variability, and acute episodic nature of visceral pain, particularly during intimate functions or acute flares that often lead to emergency department visits despite being brief and difficult to study in controlled settings [3,9]. In clinical practice, the challenge arises when diagnostic investigations fail to reveal an organic cause for pain perceived to originate from the viscera. Syndromal disorders, named after the presumed pain origin, often dissociate pain from the underlying organ pathology [10], such as persistent pain in inflammatory bowel disease during remission or pain in polycystic kidney disease that does not correlate with kidney size.

The relationship of visceral pain with broader pain syndromes, such as fibromyalgia, is also poorly understood. For some patients, managing visceral pain can alleviate fibromyalgia symptoms, yet not all fibromyalgia patients experience visceral pain, and the reasons for this disparity are unclear. Similarly, conditions like migraine, myofascial syndromes, and complex regional pain syndromes have been linked to visceral pain, but the nature and meaning of visceral pain in these contexts are not well quantified [11,12].

The development of digital tools, wearable sensors, and home point-of-care testing offers new opportunities to study visceral pain in real-world settings. These technologies enable continuous monitoring of pain and related physiological parameters, providing insights that were previously unattainable in hospital or laboratory settings [13,14]. By capturing data in everyday environments, wearable sensors can track fluctuations in visceral pain intensity and correlate them with physical activities, posture, and physiological changes such as heart rate and respiratory patterns. This allows for a more comprehensive understanding of pain triggers and patterns, offering the potential to personalize pain management strategies. The continuous nature of this data collection also facilitates early detection of visceral pain flares, enabling timely interventions and reducing the need for hospital visits.

Visceral pain may also result from unidentified pathophysiological processes within the viscera or from abnormal sensitization of the ‘pain pathway’ within the sensory nervous system, a complex signalling network relaying information from peripheral tissues via the spinal cord to the brain. Thus, visceral pain is assumed to originate from the activation of nociceptors, specialised nerve fibres that sense pain in thoracic, pelvic, or abdominal organs. Sustained nociceptive input can then lead to neuroplastic changes in the central nervous system (CNS), altering neural circuits and potentially increasing pain sensitivity and persistence over time [15]. Conversely, the role of other peripheral nerves, such as the sympathetic and vagus nerves, in detecting, localizing, and perpetuating visceral pain remain largely unknown.

Most current drugs used to treat visceral pain primarily target neuroplastic changes in the CNS, and many are even prescribed “off-label” for this purpose. However, new evidence suggests these treatments may be ineffective or harmful in some conditions, such as endometriosis [16] or narcotic bowel syndrome [17]. This has led to growing interest in developing medications that target visceral nociceptors [18], with the hope of identifying effective peripheral treatments that have reduced side effects and thus improved patient outcomes.

This study represents a novel integration of real-world digital phenotyping with multi-omics approaches to investigate visceral pain. While individual components, such as wearable technology, genetic analysis, and immunological profiling have been applied separately to chronic pain research, this is one of the first comprehensive studies to systematically combine continuous physiological monitoring via wearable sensors with exome sequencing and autoantibody analysis specifically in visceral pain cohorts. This integrated approach enables simultaneous investigation of peripheral and central mechanisms, environmental triggers, and genetic predisposition within naturalistic settings, offering unprecedented opportunities to delineate visceral pain phenotypes and identify novel therapeutic targets distinct from existing musculoskeletal pain frameworks.

### Aims and endpoints

The overarching aim of this study is to deepen our understanding of chronic visceral pain by identifying and evaluating the genetic, molecular, and physiological mechanisms that contribute to this condition. We will examine these mechanisms across different participant groups, including those with extreme visceral pain, those with a lack of expected pain despite visceral disease, and healthy controls.

Our **primary objective** is to look for physiological markers (such as changes in movement, heart rate, and postural patterns) that predict or associate with visceral pain flares by examining data from wearable sensors. This will provide objective, real-time insights into how visceral pain affects day-to-day activities, and will be tested using a pre-specified statistical model and is central to the confirmatory aspect of the study.

In addition, we will undertake a series of **secondary/exploratory objectives**, which include the following key areas of investigation:

1**Genetic insights:** We aim to identify and characterize the genetic factors that underlie chronic visceral pain in specific participant cohorts, which include individuals with conditions like polycystic kidney disease, inflammatory bowel disease, chronic pancreatitis, endometriosis, and painful bladder syndrome.2**Spatial and temporal pain mapping:** We will create detailed maps of where and when individuals experience visceral pain. This includes analysing the frequency and intensity of pain reported by participants using a remote mobile app and wearable sensors that track body movement, posture, heart rate, and breathing.3**Biological sample analysis:** We will collect a variety of biological samples—blood, urine, low vaginal swabs, and faeces—from participants to explore pain mediators and modulators. This will include testing human serum in passive transfer experiments using mice to better understand the role of autoantibodies and other pain-related factors [19].4**Comparing pain groups:** We will compare participants with high levels of visceral pain, regardless of disease activity, to those with little or no visceral pain despite having active disease. These groups will be contrasted with healthy control subjects to uncover key differences in pain experience and physiology.

The **primary endpoint** will focus on preliminary analysis of the wearable sensor data. We will assess the relationship between wearable sensor parameters (such as heart rate variability, physical activity, and posture) and self-reported pain intensity in participants with chronic visceral pain. We aim to determine whether specific physiological markers—such as body posture— can reliably predict or associate with pain levels. This analysis will provide clinically useful insights into how wearable sensor data can be used to quantify and monitor visceral pain in real-time.

The **secondary endpoints** will focus on exploratory analyses, including:

Pinpointing the functional pathways involved in the development and progression of chronic visceral pain through genetic analysis. This will help us understand why some individuals develop severe pain while others do not, even with similar disease activity.Identifying genetic variants that may regulate visceral pain, particularly in individuals whose pain severity does not align with the activity of their disease. This analysis will explore both known and novel genetic factors that contribute to pain perception.Investigating the presence and concentration of autoantibodies to explore their potential role in chronic visceral pain and immune-mediated mechanisms that may contribute to pain persistence.Identifying distinct clinical phenotypes of visceral pain using clustering techniques to group participants by shared characteristics, such as disease type, pain severity, and wearable sensor data. These clusters will be analysed for potential genetic or immune-related differences.Exploring pain frequency, location (using body maps), and time-series data from self-reported pain ratings to uncover patterns that can help characterize visceral pain flares.

By studying these diverse participant groups and collecting detailed physiological, genetic, and self-reported data, this research aims to provide new insights that could lead to improved diagnostics, treatments, and future studies on chronic visceral pain.

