### Primary endpoint analysis

The primary hypothesis we will test is that specific physiological parameters measured by wearable sensors (such as heart rate, physical activity, or respiration) will associate with self-reported pain intensity and specific body postures, such as sitting or lying down. We hypothesize that:

Higher pain scores will associate with reduced mobility and specific postures (e.g., sitting or lying down).Wearable sensor data will provide objective measures that can predict or associate with self-reported pain intensity.

This hypothesis will be tested using a linear multiple regression model with the following four predictors:

1Heart Rate Variability2Physical Activity (as measured by accelerometery)3Posture (sitting, standing, lying down)4Mean daily respiration rate

We expect that a sample size of n = 100 exclusively for the wearable sub-study provides 80% power to detect a moderate effect size (f² = 0.12 or larger) at p < 0.05, assuming four predictors.

For the primary analysis, we will fit a multiple linear regression model with mean daily visceral pain intensity as the dependent variable and the four pre-specified wearable predictors as independent variables. Model diagnostics will include inspection of residual-versus-fitted plots, Q–Q plots, and tests to assess both normality of residuals and multicollinearity between predictors. If substantial non-linearity or heteroscedasticity is detected, we will explore appropriate transformations of predictors or outcome while retaining the same pre-specified predictor set. All analyses will be conducted using validated statistical packages (either in R or Python), and the final model specification, diagnostics, and code will be documented to support reproducibility.

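### The primary model can show between-person association only, but the article also describes it as informing prediction, real-time monitoring and flare detection

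*Protocol article*

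**What the plan says.** **Purpose.** In Aims and endpoints, the primary objective is to find markers that predict or associate with pain flares, and this is called central to the confirmatory part of the study. The primary endpoint asks whether markers "can reliably predict or associate with pain levels". It then says, without qualification, that the analysis will give clinically useful insight into "how wearable sensor data can be used to quantify and monitor visceral pain in real-time". Primary endpoint analysis repeats the aim as a hypothesis: "Wearable sensor data will provide objective measures that can predict or associate with self-reported pain intensity". The same section rejects sleep metrics as a predictor because they do not suit what it calls the primary aim of detecting flares in real time.

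**Analysis.** "This hypothesis will be tested using a linear multiple regression model with the following four predictors": heart rate variability, physical activity, posture and mean daily respiration rate. Where a participant has several valid days, each predictor is first averaged over the observation period, and the average enters the primary model. The stated use of the model is to evaluate associations. Mixed models at day level, with a random intercept, will be explored.

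**Size.** "a sample size of n = 100 exclusively for the wearable sub-study" is said to give 80% power for f² = 0.12 "at p < 0.05, assuming four predictors".

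**The concern.** Two different questions share one hypothesis. *Associate* asks whether average pain differs between people with different average sensor values. *Predict*, *quantify*, *monitor* and *detect flares in real time* ask whether sensor readings give usable information about a person not yet seen, or about one person's changes over time. The confirmatory model addresses the first question only.

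Because the hypothesis joins the two with *or*, a positive association test satisfies it as worded. A reader of the results could then take the predictive and monitoring aims as supported, although the confirmatory analysis never examined them.

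**Working it through.** **1. The plan's own figure.** Inputs from Primary endpoint analysis: n = 100, four predictors, f² = 0.12, α = 0.05. The planned R² is 0.12/1.12 = 0.107. For the overall F test with df 4 and 95 and noncentrality f²·n = 12, power is 78.0% against the stated 80%. The difference is small (f² = 0.1254 would give 80%) and does not drive this point.

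**2. What the model can see.** After averaging, each predictor has one value per participant. All variation in the predictors is therefore between people. No coefficient, R² or p-value from this model carries information on whether a person's pain rises when that person's own readings change. This follows from the design and needs no arithmetic.

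**3. Fit at the significance threshold.** The critical F(4, 95) is 2.467.
- In-sample R² = 4F/(4F + 95) = 9.87/104.87 = 9.4%.
- Adjusted R² = 1 − (1 − 0.0941) × 99/95 = 5.6%.
- Stein's formula for out-of-sample R² gives 0.6%, Browne's 3.8%.
- The 95% interval for the population R² is 0 to 18.5%.
- If posture enters as three categories (five terms), R² is 10.9% and adjusted R² 6.2%.

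**4. In-sample against leave-one-out fit.** Simulation: 20,000 datasets per setting, n = 100, independent normal predictors. Leave-one-out R² is measured against the leave-one-out mean.

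| Setting | In-sample R² | Leave-one-out R² |
|---|---|---|
| Planned effect, 4 terms (mean) | about 14% | about 7% |
| Planned effect, 5 terms (mean) | 15.0% | 5.6% |
| Result just at p = 0.05, 4 terms | 9.4% | about 1.6% |
| Result just at p = 0.05, 5 terms | 10.9% | 1.4% |

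With no true effect, in-sample R² averages k/(n − 1) = 4/99 = 4.0%. At the planned effect the excess over the true value is about 14.2 − 10.7 = 3.5 points.

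**5. True performance in new participants, by size of effect.** The true effect is unknown, so a range is shown (four terms).

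| True R² | Significant | Mean in-sample R² if significant | Significant results with out-of-sample R² ≤ 0 |
|---|---|---|---|
| 3% | 24% | 12.8% | 96% |
| 5% | 40% | 13.5% | 59% |
| 10.7% (planned) | 77% | 16.5% | 5.5% |

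**6. Size in pain units.** Even if the planned effect held exactly, the residual SD would be √(1 − 0.107) = 0.945 of the pain SD, so typical error falls by only 5.5%.

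**The case against.** The case on the other side is substantial.

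- **The wording is hedged.** The endpoint is an aim to find out whether markers predict *or* associate, and the analysis is called preliminary. The Abstract speaks of correlation, and Primary endpoint analysis says the regression evaluates associations. A reader might infer that the plan promises markers that reliably predict pain. It does not. This stands, but the sentence on quantifying and monitoring pain carries no such hedge, and the real-time aim is used to justify the choice of predictors.
- **No success rule is stated.** The p < 0.05 appears only in the sample-size sentence. A reader might infer that significance alone is the evidence and entitles the authors to claim prediction. The article does not say so, and it also commits to correlations, regression analyses, diagnostics and sensitivity analyses. This stands.
- **Validation may sit elsewhere.** Cross-validation and error measures are commonly left to an analysis plan, which is not shown. Their absence from the article is no finding. The point rests on the mismatch between the stated purpose and the model that the article fixes.
- **Near-zero prediction is not the general case.** A reader might infer that any significant result is compatible with almost no predictive ability. That describes results near the threshold or small true effects. At the planned effect, out-of-sample R² averages about 6%, and only 5.5% of significant results are at or below zero.

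None of this lets a model on participant averages speak to real-time monitoring.

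**Conclusion.** The point holds as a mismatch between the claims and the confirmatory model. The between-person limitation is certain, because it follows from averaging each predictor to one value per participant. The overstatement of predictive ability is moderate: about 14% in-sample against about 7% leave-one-out at the planned effect, and 9.4% against about 1.6% for a result just reaching p = 0.05.

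These figures assume 100 complete participants, independent normal predictors and four model terms; five terms widen the gap slightly. The documents do not support the stronger conclusions that the plan promises reliable prediction, that it makes p < 0.05 the test of prediction, or that it wrongly omits a validation plan. The change is worth making before analysis, because it alters what a positive primary result may be said to show.

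**What to change.** 1. **Primary endpoint analysis.** Beside the in-sample R², report leave-one-participant-out R² and mean absolute error (in points on the 0–10 scale) against an intercept-only model. Choose any transformation inside the loop. Rest any statement about prediction on these figures, and read it as prediction of a new participant's average pain.
2. **Aims and endpoints, and Primary endpoint analysis.** State that the primary test supports between-person association only. Remove the prediction and real-time monitoring wording from what the primary model is said to show, or tie it to the day-level mixed models, labelled exploratory. To speak to within-person change, those models must separate each person's mean from the daily deviation.

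Do not require a confidence interval for the cross-validated gain to exclude zero before using the word *predict*. At the planned effect about 6% of studies would meet that rule, against 77% with a significant F test. Meeting it would still not justify a monitoring claim, since cross-validating participant averages remains between-person.

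The cost is wording and a few lines of code, with no new data or participants. Study status reports that analysis has not begun, so the change can still be pre-specified. The downside is that the reported performance and the permitted claim become less favourable.

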### Methods and analysis

This study is designed to explore chronic visceral pain through the recruitment and analysis of three distinct cohorts: **Extreme Visceral Pain** (individuals with high pain despite low disease activity), **Lack of Visceral Pain** (those with low or no visceral pain despite high disease activity), and **Healthy Controls** (from volunteers). This multi-faceted approach will allow us to examine the complex relationships between pain, disease activity, and biological markers, providing new insights into the mechanisms of chronic visceral pain. Each cohort will undergo tailored assessments, with the primary goal of identifying functional pathways that differentiate pain experiences across these diverse groups.

